# Contact

Serious adverse events and adverse events required to be reported in the expedited procedure are recorded by the physician within 24 h in the AE documentation of the eCRF and sent (automatically) to the Drug Safety Department of Roche Pharma AG (see Section 7.5). Furthermore, a pregnancy must be documented within 24 h and reported by email (or by fax) in English to the Drug Safety Department of Roche Pharma AG using the Pregnancy Report Form (Annex 14.3).

In the event of technical failure of the eCRF, please use the bilingual AE report form "Adverse Event Form" (see Annex 14.2) to report the events in Section 7.5 and send it within 24 h by email (or by fax) in English to the following address:

# List of abbreviations

| Abuse | According to Directive 2001/83/EC, Article 1, Paragraph 16 "persistent or sporadic intentional excessive use of medicinal products which is accompanied by harmful physical or psychological effects." |
| --- | --- |
| AE | Adverse Event |
| AMG | German Medicines Act |
| AMS | Drug Safety Department |
| Occupational exposure | This refers to occupational exposure to a medicinal product for human use |
| CRF | Case Record Form |
| DCC | Drug Counselling Centre |
| EoFU | End of Follow-up |
| EOT | End of Treatment |
| EVR | Early Virological Response |
| JFC | Joint Federal Committee |
| HCV | Hepatitis C Virus |
| HIV | Human Immunodeficiency Virus |
| IU | International Units |
| Medication error / unintentional | Medication errors and potential medication errors are all avoidable events which cause / could cause or could lead to unsuitable incorrect use of medications or harm to patients while the medication is under the control of a health care professional, the patient or the consumer. |
| Misuse | Improper use or deliberate misuse is the persistent or sporadic, intentional and excessive use or misuse in a manner not in conformity with the product information or established medical practice or which has no relation to it. |
| NIS | Noninterventional study |
| QMS | Quality Management System |
| RVR | Rapid Viral Response |
| SAE | Serious Adverse Event |
| SVR | Sustained Virological Response |
| Overdose | An overdose is the administration of a dose of a medicinal product (single administration or cumulative dose) which is above the maximum recommended dose approved in the marketing authorization. |

# Synopsis

| AIMS/CTMS No.: | ML21645 – Amendment 2 |
| --- | --- |
| Title: | Noninterventional study for quality assurance in therapy of chronic hepatitis C with Peg-(40kd)-Interferon alfa-2a (Pegasys) and ribavirin (i.e. Copegus) at hepatology centers – a project in cooperation with BNG (Association of German resident Gastroenterologists, part III) |
| Version and Date: | 4.3 of 28.02.2013 |
| Sponsor: | Roche Pharma AG, Grenzach-Wyhlen |
| Objectives: | Indication: chronic hepatitis C  Medication: peg­interferon alfa-2a (PEGASYS), Ribavirin (COPEGUS)   - The main objective is to determine efficacy and safety of chronic hepatitis C treatment with peg­interferon alfa-2a (Pe­ga­sys®) – usually in combination with ribavirin (Cope­gus®) – in patients treated by gastroenterology specialists in real-life setting. A descriptive comparison of the col­lected data with existing safety data and data from the approval of peg­interferon alfa-2a (Pegasys®) alone or in combination with ribavirin (Copegus®), will further establish the feasibility of the products in day-to-day practice. - In addition, information on hepatitis C therapeutic habits and patient compliance will be gained. Quality of treatment will be assessed by comparing data from clinical studies with data from physicians’ practice. Furthermore, the quality of treatment in physicians’ practices and hospital outpatient departments will be contrasted. - Direct measures will be developed –in accordance with existing treatment recommendations (SPC, consensus recommendations) – to improve the quality of care for patients with hepatitis C. These measures are training courses, direct notifications on guideline-conform treatment during the documentation of patient data, periodic analyses of data to determine the current status, and, if great deviations from the recommended therapy are observed, by project participant’s supervision. - Cause analyses and analyses of errors made by participating physicians in practices or outpatient departments will be performed to optimize the overall support quality for the therapy of hepatitis C with peg­interferon alfa-2a (Pegasys®) and ribavirin (Copegus®).   Data will be systematically collected to further refine the safety profile of peg­interferon alfa-2a (Pegasys®) and ribavirin (Copegus®). |
| Selected patient population: | Therapy data from patients over 18 years of age, with a diagnosed chronic hepatitis C with detectable virus replication and no contraindication for the use of peg (40kDa)-interferon alfa-2a (Pegasys®) or combination therapy with ribavirin (Copegus®), can be documented (please see product information).  Women of childbearing potential should use adequate contraception. It is important that female patients of childbearing potential and their sexual partners use 2 contraceptive methods at the same time during treatment and 4 months after treatment discontinuation. During this time pregnancy tests have to be performed monthly.  Particular attention is also required and pregnancy should be avoided 7 months after treatment discontinuation in female sexual partners of male patients taking ribavirin (Copegus®). Both should use adequate contraception.  Ribavirin (Copegus®) must not be used in pregnant women.  Please see the current German product information. |
| Planned number of patients: | 9000 |
| Selected physician population: | Participation is open to all physicians familiar with interferon therapy in Germany. |
| Planned number of centers: | 600 |
| Selection criteria: | Selection will take place by a specialized field force. Criteria are experience of physicians in the treatment of chronic hepatitis C and a known excellent documentation quality in the past |
| Main parameters of interest: | Demographic data, anamnesis of hepatitis C, viral genotype and viral load, relevant laboratory parameters, histology (if available), concomitant diseases, data of treatment and dosage of Peginterferon alfa-2a and ribavirin and other concomitant medication, virological outcome: RVR, EVR, EOT, SVR, (severe) adverse events |
| Procedures: | Baseline, routine visits at weeks 2, 4, 8, 12, 24, 36, 48, EOT and EoFU, additional modules for HIV-coinfection, opioid substitution, cardiovascular risk, HCV after liver transplantation, and pharmacoeconomics |
| Statistical considerations: | It is planned to document at least 9000 cases in practices specialized in treatment of hepatitis and hospital outpatient departments, over a recruitment period of at least 4 years.  In Germany, 16,000 patients per year are treated with interferon therapy in practices specialized in hepatitis treatment, outpatient departments and hepatology units in hospitals. Thus, a sample size of approximately 12.5 % of all treated patients can be achieved. The sample is considered to be representative, taking into account the areal distribution of gastroenterologists in Germany. |
| Duration: | According to the product information, the duration of the combination therapy with ribavirin (Copegus®) for chronic hepatitis C depends on the virus genotype. Naive patients with virus genotype 1 and genotypes 2/3 should be treated for 48 weeks and 24 weeks, respectively. Patients with low viral load at baseline (< 800,000 IU/ml) and Rapid Viral Response (HCV-RNA undetectable after 4 weeks of treatment), can sufficiently be treated for 24 weeks only, in case of genotype 1, and for 16 weeks only, in case of genotypes 2/3.  This recommendation is identical for patients with genotype 4.  Duration of retreatment in patients who have failed prior therapy should be 48 weeks in general. In case of genotype 1 patients with prior non-response, retreatment duration of 72 weeks is recommended.  The recommended duration of Pegasys monotherapy is 48 weeks.  In clinical studies with peg­interferon alfa-2a (Pegasys®) alone or in combination with ribavirin (Copegus®) (see product information), a Rapid Viral Response was defined by a HCV RNA load below the limit of detection after 4 weeks of therapy whereas an early virological response was defined by a HCV RNA load below the limit of detection or by a reduction of the virus titre by 99 % of the initial value after 12 weeks of therapy.  Of patients with genotype 1 or 4 and no early virological response after 12 weeks therapy with peg­interferon alfa-2a (Pegasys®) alone or in combination with ribavirin (Copegus®), only a very small number (<2%) achieved sustained virological response.  In those patients, therapy should be discontinued, taking into account the low probability of a sustained virological response.  In patients with genotype 2 or 3, early virological response is known to be very high (97 %) and subsequently a high SVR rate is achieved after 24 weeks. Therefore, viral load determination after 12 weeks of treatment is not deemed to be necessary.  Planned FPI: 01/01/2008  Planned LPI: 31/12/2011  Planned LPO: 30/06/2013 |

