Treatment over 24 weeks may be considered for patients showing an infection with genotype 1 and a low initial viral load (LVL) ( 800,000 IU/ml) or with genotype 4 or who become HCV-RNA negative ( 50 IU/ml) by week 4 and remain HCV-RNA negative up to week 24 (Jensen D et al. 2006, Ferenci et al. 2006).

A total treatment period of 24 weeks, however, may be associated with a higher risk of relapse than treatment over 48 weeks. In these patients, the tolerability of the combination therapy as well as prognostic factors such as the degree of fibrosis should be taken into account when deciding the duration of treatment. In patients with a genotype 1 infection and a high initial viral load (HVL) (>800,000 IU/ml), and who become HCV-RNA negative by week 4 and remain HCV-RNA negative up to week 24, a shortening of the treatment duration should nevertheless be considered with caution because the limited data available suggest that shortening the treatment in this patient population may have a significantly negative impact on the persistent virological response.

Patients with genotypes 2 and 3 are normally treated with a duration of 24 weeks. No difference in efficacy was observed compared to a 48-week treatment.

A shortened treatment for 16 weeks may be considered for such genotype 2/3 patients who show a low initial viral load (LVL) ( 800,000 IU/ml) and who are already HCV-RNA negative in week 4 ( 50IU/ml) and remain HCV-RNA negative up to week 16.

As with the possibility of shortening the treatment period for genotype 1, the tolerability and prognostic factors should also be taken into account with genotype 2/3 when deciding on a reduction of the treatment period.

For patients with genotypes 5 and 6 less well substantiated by studies, the same recommendations are given as for the genotype 1 with HVL.

Patients with HIV-HCV coinfection should be treated over 48 weeks regardless of the genotype. A treatment period of less than 48 weeks has not been adequately researched.

The recommended total duration for retreatment of previously treated patients is 48 weeks. Patients with a detectable viral load in week 12 of the retreatment should discontinue this retreatment.

If retreatment is considered for patients who are infected with virus genotype 1 and who fail to respond to previous treatment with pegylated interferon plus ribavirin, the recommended total duration of treatment is 72 weeks.

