# Conduct of the noninterventional study

## Duration and premature termination of the noninterventional study

The noninterventional study will start on 1-Jan-2008 and is scheduled to end on 30-Jun-2014. The individual duration of the documentation of a patient is about 72 weeks.

The noninterventional study is intended to cover the entire treatment period (depending on the physician's decision and the main baseline factors such as genotype and viral load, or up to the end of treatment with peg­interferon alfa-2a (Pegasys®). Independently of the treatment decision taken, concluding documentation is to be generated for every patient even after discontinuation of treatment with peg­interferon alfa-2a (Pegasys®).

In the event of premature termination of the overall prospective noninterventional study, for example for regulatory reasons, the available data will be analyzed completed and a final report of the prospective noninterventional study will be compiled, if appropriate in a reduced form.

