#### At the end of treatment / documentation (end of therapy):

- Therapeutic consequence: reason for end / discontinuation of therapy
- Reasons for therapy discontinuation: lacking virological response, lacking tolerability, lacking compliance, unplanned event (e.g. imprisonment, detoxification), patient's wish, patient no longer attended, other reason
- Concomitant medication
- New comorbidities
- Body weight
- Hepatitis C laboratory diagnostic tests
  HCV-PCR (quantitative/qualitative), *only recommended in week 12*
  HCV-PCR (qualitative), *only recommended in week 24 for GT-2/3, only in week 48 for GT-1/4*
  (HCV-PCR (quantitative/qualitative) can be documented in week 4, 8, 12, 24 and 48)
- Hepatitis B laboratory diagnostic tests (only if chronic hepatitis B was documented at the baseline examination): HBsAg (+/-), HBeAg +/-; HBV-DNA quant./qual., anti-HBs (+/-); anti-HDV (+/-), HDV-RNA (+/-, qual. or quant.)
- Autoantibodies: ANA, LKM, SMA, AMA, SLA, Trak, MAK, rheumatoid factors, other
- Laboratory parameters
  GPT (=ALT), GOT (= AST), GGT,
  Other laboratory parameters:
  hemoglobin, platelets, WBC, neutrophils (%), bilirubin, creatinine, TSH, blood glucose (fasting), HbA1c, triglycerides, cholesterol, HDL, LDL, serum ferritin
- Clinical symptoms: none, fatigue, fever, muscular stiffness, skin changes, hair loss, joint pain, muscle pain, abdominal pain, nausea, reflux, weight loss, headache, insomnia, irritability, restlessness, depression, depressive mood, psychosis, impaired concentration, anorexia, jaundice, pruritus, elevated GPT, craving / withdrawal-like symptoms, other;
  causal relationship with Pegasys and/or ribavirin
- Treatment-related sick leave (duration) since the last examination
- (Monthly) pregnancy test
- Adverse events (including suspected cases) with substance-specific causality survey
- Clinical assessment of the tolerability of Pegasys and the combination with ribavirin (Copegus®): very good, good, moderate, poor
- Quality of life assessment compared to before treatment: symptom-free; improved, but not symptom-free; unchanged
- Alcohol consumption no/yes, if yes, inquiry ≤/ > 40 g/d and drinks/d in the last 30 days
- Compliance (assessed by the physician):
   very good: all medications taken
   good: max. 10% not taken
   satisfactory: max. 20% not taken
   poor: > 20% not taken
- Quality of life assessment compared to before treatment: symptom-free; improved, but not symptom-free; unchanged

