## Public study registry and publication

The noninterventional study is published in a public study registry prior to its commencement. The summary of results is to be published at the latest one year after completion (last patient / last visit) of the noninterventional study (e.g. publication and presentation at scientific congresses). This is done in consultation between the Scientific Director of the noninterventional study and Roche Pharma AG. However, this does not mean that either of the partners has the right to censor or withhold the publication.

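### The synopsis puts last patient out a year before the study end in Section 6.1, too early for SVR after a 72-week course started late in recruitment

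*Protocol*

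**What the plan says.** The Duration row of the synopsis gives three planning dates: "Planned FPI: 01/01/2008", "Planned LPI: 31/12/2011" and "Planned LPO: 30/06/2013". Section 6.1 reads: "The noninterventional study will start on 1-Jan-2008 and is scheduled to end on 30-Jun-2014". Both stand in current text, not in a change log.

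The synopsis and Section 4.1.3 describe treatment courses from 16 to 72 weeks. For genotype 1 patients who did not respond to earlier pegylated interferon plus ribavirin, Section 4.1.3 says "the recommended total duration of treatment is 72 weeks". The synopsis lists SVR among the main parameters, and Section 7.2.2 provides a record at week 24 of follow-up with an HCV-PCR entry.

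Section 6.1 puts documentation at about 72 weeks per patient. Section 6.2 places final documentation in general 48 to 72 weeks after the start, or at the end of treatment if that comes first.

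In Section 7.2.2, the end-of-treatment record lists HCV-PCR. For the qualitative test it adds "only recommended in week 24 for GT-2/3, only in week 48 for GT-1/4", and it names weeks 4, 8, 12, 24 and 48 as those in which PCR can be documented.

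**The concern.** Two dates a year apart appear to describe the same milestone. Section 10.4 counts the publication deadline from "completion (last patient / last visit) of the noninterventional study", so the end of the study and last patient out should coincide. The report in Section 9 is also due within 12 months of the end of the study, so both deadlines depend on which date is used.

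The earlier date also looks too short for the longest course in the protocol. If it were applied, the missing SVR results would not be a random subset. They would fall only on long courses begun late in recruitment, which the protocol describes for patients who had already failed treatment. The documentation lengths in Sections 6.1 and 6.2 point the same way, since both appear to be built around a 48-week course plus follow-up.

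The timing was still open when this version was written. It is dated 28.02.2013, and a 72-week patient enrolled on the last day would have remained on treatment until 18 May 2013.

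**Working it through.** This is calendar arithmetic only.

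**Inputs.** First patient in 1 Jan 2008, last patient in 31 Dec 2011 and last patient out 30 Jun 2013 (synopsis). Study end 30 Jun 2014 (Section 6.1). Course lengths of 16, 24, 48 and 72 weeks (synopsis, Section 4.1.3). Follow-up of 24 weeks (Section 7.2.2). Assumptions: treatment starts on the day of inclusion, and SVR is read at follow-up week 24; the protocol does not spell out the SVR time point.

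**Reproducing the plan's figures.** 48 + 24 = 72 weeks, the documentation length in Section 6.1. Last patient in + 72 weeks = 18 May 2013, which is 43 days before the synopsis date. The synopsis date is last patient in plus 18 months: 547 days / 7 = 78.1 weeks. It is therefore consistent with a 48-week course.

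**Each course, for a start on 31 Dec 2011** (documentation needed = course + 24 weeks):

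| Course (weeks) | Documentation (weeks) | Follow-up week 24 | Relative to 30 Jun 2013 |
|---|---|---|---|
| 16 | 40 | 6 Oct 2012 | 267 days before |
| 24 | 48 | 1 Dec 2012 | 211 days before |
| 48 | 72 | 18 May 2013 | 43 days before |
| 72 | 96 | 2 Nov 2013 | 125 days after |

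**Longest course that fits for the last patient.** Synopsis date: 78.1 − 24 = 54.1 weeks. Section 6.1 date: 912 days / 7 = 130.3 weeks, and 130.3 − 24 = 106.3 weeks. The later date covers every course described, with 240 days to spare after 2 Nov 2013.

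**Starts exposed under the synopsis date.** 30 Jun 2013 − 96 weeks = 28 Aug 2011. From there to 31 Dec 2011 is 125 days. Recruitment runs 1,461 days, and 125 / 1,461 = 8.6%. A 72-week course begun on the last day would be only 43 days past end of treatment when the study closed.

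**Documentation window.** A 72-week course needs 96 weeks, which is 24 more than Section 6.1 states and 24 beyond the upper limit in Section 6.2. Read literally, Section 6.2 makes the final record for that patient no later than week 72, the end of treatment, before SVR can be assessed. Section 7.2.2 nevertheless provides a follow-up record 24 weeks later, so the sections disagree. The 40 weeks of a 16-week course also lie outside the 48-to-72-week window, on the short side.

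**PCR week list at end of treatment.** Weeks 24 and 48 are named as documentable. Weeks 16 and 72, the ends of the shortest and longest courses described, are not.

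**The case against.** The strongest defence is that no data need be lost. Section 6.1, the operative text, carries the later date, which accommodates every course. It also says that the study covers the whole treatment period and that every patient receives concluding documentation. The two dates might mark different milestones, and the documentation lengths are worded as approximate or usual. The 8.6% is a share of recruitment days and applies only to 72-week courses. If 5% to 10% of patients had such courses (an assumption) and recruitment were even, 0.4% to 0.9% of all patients would be exposed. Fewer still would reach week 72, since Section 4.1.3 has retreated patients with detectable virus at week 12 stopping.

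The point about size stands. The rest does not remove the contradiction. A reporting year cannot explain the gap, because Section 9 counts its 12 months from the end of the study. Even as a separate milestone, a last-patient-out date of 30 Jun 2013 is too early for a course the synopsis itself lists. Approximate wording does not stretch 72 weeks to 96.

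A reader might infer three stronger things that the protocol does not support:

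- **That the visit schedule fits only 24- and 48-week courses.** The end-of-treatment and follow-up visits are listed separately from the fixed weeks and move with treatment length, so 16- and 72-week patients have both.
- **That relapse cannot be told from non-response.** HCV-PCR is an item on the end-of-treatment record and on the follow-up record. It can be entered at several on-treatment weeks, and lack of virological response is a recorded reason for stopping. Section 4.3 leaves testing to the physician and Section 7.2 asks that results obtained be documented completely, so a week label does not imply a missing result.
- **That a further form is needed after week 48.** Section 7.4 has adverse events documented throughout, including follow-up. An added form would be a preference, not the correction of an error.

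**Conclusion.** The protocol is wrong as written on two linked points. It gives two end dates 365 days apart without explanation. The earlier one falls 125 days before follow-up week 24 for a 72-week course started on the last recruitment day. If it were applied, 72-week courses started after 28 Aug 2011 would lose SVR. The documentation lengths in Sections 6.1 and 6.2 fall 24 weeks short of what such a patient needs.

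The loss is conditional on the synopsis date being used. The number of patients cannot be computed, because the share on 72-week courses is not given; it is probably a small part of the 9,000 planned. The result rests on treatment starting at inclusion and SVR being read at follow-up week 24. No view is taken on any treatment duration. The correction is worth making because it is nearly free and protects a main parameter in a group that would otherwise be lost selectively.

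**What to change.** - Use one date for last patient out and study end in the synopsis and Section 6.1, no earlier than last patient in plus 96 weeks (2 Nov 2013). The 30-Jun-2014 date already in Section 6.1 qualifies. If two milestones are intended, define each and keep last patient out on or after 2 Nov 2013. The report and publication deadlines then follow from that date without further change.
- Reword the documentation length in Section 6.1 and the final-documentation rule in Section 6.2, so that final documentation falls at follow-up week 24 after the patient's actual end of treatment, whatever the course length.
- As a minor wording change, label the HCV-PCR entry on the end-of-treatment record in Section 7.2.2 as belonging to the actual end of treatment, since weeks 16 and 72 are missing from its list. This concerns where a result is filed, not whether a test is done.

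The cost is one date and a few sentences. No visit, form or test is added.
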